### Primary endpoint

The primary endpoint is the percentage of detected IOP peak values. Fluctuations and peak values of IOP are considered as a patient-relevant outcome that can be associated with glaucoma progression and warrant adjustment of therapy [15–18].

In the IG, the primary endpoint will be measured by the patients themselves for each eye using an IcareHOME® self-tonometer at six predefined times (6 a.m., 8 a.m., 12 a.m., 4 p.m., 8 p.m. and 12 p.m.) for 7 days (see Table 2). The measurements at 6 a.m. and 12 p.m. will count as night measurements. The night measurements are performed in sitting position, preferably without standing up before. The exact time is recorded electronically. One measurement sequence is based on six individual readings. The IcareHOME® devices calculates the final IOP measurement by discarding the highest and lowest readings and only displaying the mean of the remaining four readings [19]. In the CG, clinical staff will measure the IOP of the patients over at least 24 h at the same times of day and night using rebound tonometry or GAT. To compare these measurements with the IcareHOME®, six readings will be obtained for each eye and the mean of these values will be used for analysis, after discarding the highest and lowest readings.

**Table 2 Tab2:** Study endpoints

Study endpoints	Instruments	Time of assessment						
		*T*_−1_	*T*_0_	*T*_1_	*T*_2_	*T*_3_	*T*_4_	*T*_5_
Patient-related endpoints								
Health-related quality of life	EQ-5D questionnaire		X					X
Clinical endpoints								
IOP fluctuation and peak values	Outpatient/inpatient IOP monitoring	X	X	X*	X	X	X	X
VFI	Standard automated perimetry		X				X	X
MD	Standard automated perimetry		X				X	X
PSD	Standard automated perimetry		X				X	X
Retinal nerve fiber layer thickness	OCT/HRT		X					X
Rim volume	OCT/HRT		X					X
Rim area	OCT/HRT		X					X
Blood pressure (RR)	24 h blood pressure measurement			X*				
Economic endpoints								
Resource utilization (outpatient and inpatient)	Service providers/statutory health insurers	12-month course						
Costs	Service providers/statutory health insurers	12-month course						
Days of incapacity to work (unspecific and diagnosis-specific)	Surveys/statutory health insurers	12-month course						
Sick pay days	Surveys/statutory health insurers	12-month course						
Formative assessment								
Implementation-promoting and inhibiting factors	Interviews, questionnaire	During or at end of project						
Usability	Interviews, questionnaire	During or at end of project						

^***^*Measurement of IOP and blood pressure will be performed either during inpatient stay in participating hospitals (CG) or at home (IG. The blood pressure monitor will be put on in hospital and should be worn at home, while self-tonometry is performed by patients themselves over a time frame of 7 days)*

*Time stamps:*

*T*_*−1*_*:* Enrolment of patients by local ophthalmologists

*T*_*0*_*:* Initial examination in a participating hospital

*T*_*1*_*:* For IG: consultation with local ophthalmologist for evaluation of data from self-tonometry and 24-h blood pressure measurement; for CG: hospital admission for IOP measurements and 24-h blood pressure measurements

*T*_*2*_*:* First check-up examination at a local ophthalmology practice after 3 months

*T*_*3*_*:* Second check-up examination at a local ophthalmology practice after 6 months

*T*_*4*_*:* Third follow-up examination at a local ophthalmology practice after 9 months

*T*_*5*_*:* Final examination in a participating hospital

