**Methods:**

The SALUS study is a randomized controlled, open non-inferiority trial, alongside an economic analysis, determining whether outpatient monitoring of IOP with self-tonometry is at least as effective as current standard care and would reduce treatment costs. Participants (*n* = 1980) will be recruited by local ophthalmologists in the area of Westphalia-Lippe, Germany, and randomized to receive 7-day outpatient or 24-h inpatient monitoring. Participants in both study arms will also receive 24-h blood pressure monitoring. Furthermore, patient data from both study groups will be collected in an electronic case file (ECF), accessible to practitioners, hospitals, and the study participants. The primary endpoint is the percentage of patients with IOP peaks, defined as levels 30% above the patient-specific target pressure. Data will also be collected during initial and final examinations, and at 3, 6, and 9 months after the initial examination.

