More specifically, the SALUS study aims to demonstrate that self-tonometry is non-inferior to the established 24-h inpatient IOP measurements for monitoring and treating glaucoma. The primary hypothesis in this non-inferiority trial is that the percentage of patients in whom pressure peaks could be detected during the pressure profile would not differ significantly between the intervention group (IG = outpatient self-tonometry) and the control group (CG = inpatient measurement every 3 h over the course of 24 h). In this study, a pressure peak was defined as a level 30% above the patient-specific target pressure which will be set by the treating ophthalmologists. The health economic hypothesis tests whether the use of self-tonometers reduces costs from a healthcare provider perspective compared to current standard care.

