### Randomization

After informed consent, patients will be randomized 1:1 into the IG and CG. The randomization will be generated automatically by the ECF after the local ophthalmologist has submitted the patient’s master data (year of birth, sex, and three digits of the zip code) and eligibility criteria in a web-based form. The underlying randomization sequence will be known only to the developers of the ECF (Fraunhofer Institute for Applied Information Technology FIT) who will act independently of the personnel analyzing (Bielefeld University) and conducting (University of Muenster Medical Center) the study. This sequence will be concealed from all study staff so that it cannot be manipulated by physicians, clinical staff, or the patients themselves.

Participants will receive a study identification number after randomization and their assignment to one study group. Owing to the nature of the intervention, it will not be possible to blind either the patients, the personnel conducting the study or the healthcare providers. The independent evaluators of the study will be blinded during the study by being provided solely with a pseudonymized data set for data analysis.

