### Sample size

The sample size was determined using the license-free software “R” (R v. 3.6.3, Rstudio v. 1.2.5042). The estimation of sample size and power analysis is based on the primary endpoint “exceeding patient-specific target pressure”. As null hypothesis, it is assumed that the proportion of pressure peaks in IG is smaller than the proportion in CG (i.e., non-inferiority).

Based on clinical experience, a margin of 20% is assumed for detection of IOP fluctuations and peak values in both groups. A non-inferiority margin of *δ* = 0.05 is acceptable, meaning the proportion of pressure peaks in self-tonometry should fall below the proportion in 24 h IOP by more than 5% to be taken as a statistically significant difference [34, 35]. With regard to the probability of type I and II errors, significance levels will be set at *α* = 0.05 and *β* = 0.2, respectively, i.e., a power of (1 − *β*) = 0.8. This results in a total of 1584 patients (792 per group). After adjusting for a drop-out rate of 20%, a final sample size of 1980 patients (990 per group) will be required for this trial (see Fig. 2).

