### Statistical analyses

All statistical analyses will be performed using the current version of R/Rstudio and results will be presented following the CONSORT recommendations [36, 37]. Baseline characteristics (including sociodemographic and clinical data) will be analyzed using appropriate descriptive methods. These will include absolute and relative frequency distributions and measures of dispersion, such as median, mean, quantile, variance or standard deviation, used as appropriate, and visualized in a suitable form (e.g., boxplot or histogram). More precisely, baseline characteristics will be summarized for the IG and CG. Standard deviation (when assuming a Gaussian distribution), median, and interquartile ranges will be applied for continuous data (e.g., VFI or blood pressure) and frequencies or percentages will be used for binary data. After analyzing the entire cohort, subgroup analyses will be conducted to determine potential effect modifications (e.g., time effects, age or gender) on the primary endpoint.

The primary endpoint, percentage of detected peak values in IOP, will be analyzed using suitable inferential statistic methods (e.g., Mann–Whitney-*U* test for independent samples and assuming a normal distribution or odds ratios for binary outcomes). An appropriate regression model will be used to evaluate which regressor has an influence on the primary endpoint and residual analysis will be applied to test the results of the model for significance. Secondary endpoints will be evaluated using a similar analysis strategy while using appropriate models for the outcomes.

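### The primary endpoint is worded inconsistently in unit and threshold, so the article does not fix which quantity the 20% planning rate and the analysis refer to

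*Protocol article*

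**What the plan says.** Three wordings of the primary endpoint stand in the article.

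- **Per patient, 30% above target.** Abstract, Methods: "The primary endpoint is the percentage of patients with IOP peaks, defined as levels 30% above the patient-specific target pressure". The Introduction states the primary hypothesis in the same unit ("the percentage of patients in whom pressure peaks could be detected during the pressure profile would not differ significantly") and gives a definition for the whole study: "In this study, a pressure peak was defined as a level 30% above the patient-specific target pressure".
- **Peak values, unit not stated.** Primary endpoint section: "The primary endpoint is the percentage of detected IOP peak values". Statistical analyses: "The primary endpoint, percentage of detected peak values in IOP, will be analyzed using suitable inferential statistic methods". The examples that follow are a Mann–Whitney U test and, for binary outcomes, odds ratios.
- **Target exceeded, no 30%.** The Sample size section gives the endpoint on which the calculation rests as "exceeding patient-specific target pressure". It then attaches the 20% to detection of IOP fluctuations and peak values, and words the hypothesis as a proportion of pressure peaks.

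The Primary endpoint section has patients in the intervention group (IG) measure each eye at six set times a day for 7 days. In the control group (CG), staff measure at the same times over at least 24 hours. The threshold depends on a "patient-specific target pressure which will be set by the treating ophthalmologists". The Randomization section lists the data entered before allocation as "year of birth, sex, and three digits of the zip code) and eligibility criteria in a web-based form".

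**The concern.** The wordings differ in two respects that affect the result. One is the unit: patients with a peak, or peak values out of some denominator that could be patients, eyes or readings. The other is the threshold: 30% above target, or the target itself.

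The unit matters more than usual because the arms are sampled very unequally. More readings give a patient more chances to show at least one peak, but do not by themselves change the share of readings that are peaks. The threshold matters because exceeding the target is at least as frequent as exceeding it by 30%, and the required sample size depends on the event rate.

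This goes beyond detail that an analysis plan could add, because the article's own sections disagree on the primary endpoint. If that stays open in an open-label trial, the definition could be settled after results by arm are visible.

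**Working it through.** **1. The stated sample size.** Inputs from the Sample size section: rate p = 0.20 in both groups, margin δ = 0.05, α = 0.05, power 0.80, drop-out 20%. Sidedness is not stated; one-sided is assumed.

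n per group = 2p(1 − p)(z₀.₉₅ + z₀.₈₀)² / δ² = 2 × 0.16 × (1.645 + 0.842)² / 0.0025 = 0.32 × 6.1826 / 0.0025 = 791.4, rounded up to **792**.

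Total 2 × 792 = 1584, and 1584 / 0.8 = **1980**. All three stated figures reproduce. (One-sided 2.5% would give 1005 per group.) The formula takes one yes/no outcome per patient. It fits the Abstract and Introduction, and not a share of clustered readings.

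**2. If the 20% belongs to another definition.** The article gives no rate for each definition, so the rates below are assumptions. Power at 792 per group = Φ(δ / √(2p(1 − p)/792) − 1.645).

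| Assumed common rate | n per group for 80% power | Total with 20% drop-out | Power at 792 per group |
|---|---|---|---|
| 10% | 446 | 1115 | 95% |
| 20% | 792 | 1980 | 80% |
| 30% | 1039 | 2598 | 70% |
| 40% | 1188 | 2970 | 65% |
| 50% | 1237 | 3093 | 63.5% |

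For p = 0.30: √(0.42/792) = 0.02303; 0.05/0.02303 − 1.645 = 0.526; Φ = 0.70.

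**3. Patient-level against reading-level percentages.** Readings per eye: IG 6 × 7 = 42; CG about 6 (the Introduction says every 3 hours, which would be 24/3 = 8). Take one series of readings per patient. Suppose that 20% of patients show a peak within 6 readings and that both methods have the same per-reading rate.

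- Independent readings: q = 1 − 0.8^(1/6) = 3.65% per reading. Over 42 readings, 1 − 0.8⁷ = 79% of patients show a peak.
- Correlated readings (beta-binomial with mean μ and within-patient correlation ρ): P(at least one of m) = 1 − B(a, b + m)/B(a, b), with a = μ(1 − ρ)/ρ and b = (1 − μ)(1 − ρ)/ρ.

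| Assumed ρ | Per-reading rate, both arms | Patients with a peak in 6 readings | Patients with a peak in 42 readings |
|---|---|---|---|
| 0.1 | 4.6% | 20% | 52% |
| 0.3 | 6.5% | 20% | 38% |
| 0.5 | 8.9% | 20% | 32% |
| 0.7 | 12.0% | 20% | 28% |

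For ρ from 0.1 to 0.7, the reading-level difference is zero while the patient-level difference favours the IG by 8 to 32 points. The margin is 5 points.

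Conclusions can also diverge. At ρ = 0.1, let the IG per-reading rate be only 0.5%, against 4.6% in the CG. The reading-level deficit is 4.1 points, inside the margin. The same formula with m = 42 gives 7.7% of IG patients with a peak against 20% in the CG, a deficit of 12.3 points and well outside it. Wherever the control per-reading rate is below 5%, a 5-point margin on that scale cannot be missed in truth, even by a method that detects nothing.

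**The case against.** The strongest reply is that the Introduction defines a pressure peak once for the whole study and states the hypothesis per patient. Peak values and proportion of pressure peaks elsewhere can then be shorthand for that event. The sample size supports this, since it reproduces as a patient-level proportion. This largely stands for the threshold in the Primary endpoint and Statistical analyses sections. It does not supply a unit there, and the choice between a rank test and odds ratios leaves the unit open. Nor does it explain the Sample size label, which drops the 30%.

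A reader might infer more than the text supports:

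- *That the 20% and the analysis do refer to different quantities, or that the sample size is wrong.* Neither is shown. If the 20% is the patient-level rate of peaks 30% above target, 1980 stands.
- *That the endpoint section prescribes a per-reading percentage.* That is one possible reading; the section names no denominator.
- *That treating ophthalmologists set or shift targets once they know the arm.* No passage says so. Eligibility criteria are entered before randomization, and one alternative in Table 1 is failure to reach target pressure, so some patients must already have a target. The list of data entered beforehand does not name a target value, so the risk is possible but not demonstrated.

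A rule for combining two eyes may stand in a fuller document. Its absence here is not an error, but the harmonised wording should include it.

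**Conclusion.** The inconsistency is real and concerns the primary endpoint, so it must be reconciled. What is established is that the article does not fix the unit or, in the Sample size section, the threshold. The planning rate and the analysis may therefore refer to different quantities. No arithmetic error is established.

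The size depends on assumptions. Power at 792 per group is 80% at a 20% rate, 70% at 30% and 63.5% at 50%; which rate belongs to which definition is not known from the article. The 8 to 32 point gap between patient-level and reading-level results assumes equal per-reading rates, one series of readings per patient, and a within-patient correlation of 0.1 to 0.7. It illustrates that the choice of unit can decide the non-inferiority conclusion and does not predict the trial's result.

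**What to change.** - Use the patient-level binary endpoint of the Abstract and Introduction in the Primary endpoint, Sample size and Statistical analyses sections: a patient with at least one scheduled reading at least 30% above the patient-specific target. State how the two eyes are combined.
- State that the 20% is the expected rate of exactly that event. If so, the sample size stays at 1980; if not, recalculate it.
- Replace the open choice of test with one binary analysis: the difference in proportions, IG minus CG, with its confidence limit compared with −0.05. A rank test does not address that margin.
- Report any per-reading percentage only as secondary, allowing for clustering within eyes and patients.
- As a safeguard in an open-label trial, record the patient-specific target in the electronic case file form before randomization and compute the endpoint from that value.

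The cost is wording in three sections and one required field in an existing form. The unequal number of readings remains under the patient-level definition; this change makes clear what is compared but does not remove that difference.

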### Secondary endpoints

#### Clinical endpoints

Visual field indices such as visual field index (VFI), mean deviation (MD), and pattern standard deviation (PSD) will be determined using standard automated perimetry. These values will be measured on initial and final examination in hospitals and after 9 months during the follow-up visit at the local ophthalmology practice. These measurements will be used to determine the extent of visual field loss due to suspected or confirmed glaucoma. Furthermore, the values will be used to calculate visual field damage and classify stages of glaucoma [20, 21].

RNFL thickness, rim volume, and rim area will be needed to map short- and medium-term results of glaucoma diagnosis and progression within the project time-frame [22]. Those surrogates will be determined with OCT (RNFL thickness) and HRT (rim volume and area), if available, during initial and final examination in participating hospitals.

IOP will be measured on all examinations in participating hospitals and at the local ophthalmology practice. Since low ocular perfusion pressure and low blood pressure are associated with an increased risk of glaucoma, vascular factors can be of importance for further glaucoma treatment planning [23]. Measurement of blood pressure will be performed parallel to IOP monitoring during inpatient stay or at home for 24 h, every 15 min during day between 6 a.m. and 10 p.m. and every 30 min at night between 20 p.m. and 6 a.m.

Health-related quality of life will be evaluated using the EQ-5D-5L questionnaire, a generic multidimensional instrument implemented by the EuroQol Group [24, 25]. The EQ-5D is frequently used to analyze quality of life in ophthalmic diseases such as glaucoma, and glaucoma and disease progression with visual damage are known to influence health-related quality of life [26–29].

#### Health economic endpoints

Costs of healthcare services as well as resource utilization for both groups will be estimated on the basis of secondary data from the statutory health insurers participating in the SALUS study. More precisely, this will include direct costs such as those of general and specialist care from inpatient and outpatient visits, medication, therapeutic products, medical aids, and other health services related to suspected or diagnosed glaucoma. Costs associated with absenteeism will also be analyzed. Those data will be provided by the statutory health insurers. Cost effects and differences between IG and CG can then be analyzed, as well as the costs related to glaucoma progression [30, 31].

#### Formative assessment

In addition, patient-related usability and user acceptance of the IcareHOME® tonometer as well as usability and user acceptance of the ECF for healthcare providers and participants will be assessed through interviews and a questionnaire, based on the Unified Theory of Acceptance and Use of Technology (UTAUT) model [32], which will examine expectancy, effort expectancy, social influence, and facilitating conditions.

### Sample size

The sample size was determined using the license-free software “R” (R v. 3.6.3, Rstudio v. 1.2.5042). The estimation of sample size and power analysis is based on the primary endpoint “exceeding patient-specific target pressure”. As null hypothesis, it is assumed that the proportion of pressure peaks in IG is smaller than the proportion in CG (i.e., non-inferiority).

Based on clinical experience, a margin of 20% is assumed for detection of IOP fluctuations and peak values in both groups. A non-inferiority margin of *δ* = 0.05 is acceptable, meaning the proportion of pressure peaks in self-tonometry should fall below the proportion in 24 h IOP by more than 5% to be taken as a statistically significant difference [34, 35]. With regard to the probability of type I and II errors, significance levels will be set at *α* = 0.05 and *β* = 0.2, respectively, i.e., a power of (1 − *β*) = 0.8. This results in a total of 1584 patients (792 per group). After adjusting for a drop-out rate of 20%, a final sample size of 1980 patients (990 per group) will be required for this trial (see Fig. 2).

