## Materials and methods

### Study design

The SALUS study is a multicenter, two-arm parallel group, open non-inferiority, randomized controlled trial with an economic analysis alongside.

This non-inferiority design was chosen to establish that outpatient monitoring of IOP with self-tonometry is not less effective than standard care with hospitalized monitoring of IOP. The trial will be conducted in hospitals and patients’ homes in the district of Westphalia-Lippe, Germany. Each participant will be followed for 12 months from the start of the trial, with regular follow-up every 3 months by local ophthalmologists (see Fig. 1).

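### The non-inferiority hypotheses are misstated in the Introduction and in Sample size, and do not match the test that gives 792 patients per group

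*Protocol article*

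**What the plan says.** The article declares a non-inferiority trial; Study design gives its purpose as "to establish that outpatient monitoring of IOP with self-tonometry is not less effective than standard care". It then describes the hypothesis in three ways.

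- **Sample size, null hypothesis:** "As null hypothesis, it is assumed that the proportion of pressure peaks in IG is smaller than the proportion in CG (i.e., non-inferiority"). No margin appears in this sentence.
- **Sample size, meaning of the margin:** "A non-inferiority margin of *δ* = 0.05 is acceptable", which is then explained to mean that the self-tonometry proportion should "fall below the proportion in 24 h IOP by more than 5% to be taken as a statistically significant difference".
- **Introduction, last paragraph:** the primary hypothesis is that the percentage of patients with detected peaks "would not differ significantly between the intervention group" and the control group.

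The planning inputs in Sample size are: "a margin of 20% is assumed for detection of IOP fluctuations and peak values in both groups"; "significance levels will be set at *α* = 0.05 and *β* = 0.2"; 792 per group (1584 in total); and 1980 after a 20% drop-out allowance. The sidedness of alpha is not given. Statistical analyses says that model results will be presented with 95% confidence intervals, but does not relate an interval to the margin.

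**The concern.** In a non-inferiority trial the null is that the new method is worse by at least the margin, and rejecting it supports the claim. None of the three statements says this.

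- The null in Sample size has the right direction but no margin. Taken literally, rejecting it means showing that self-tonometry detects peaks at least as often as inpatient monitoring, with no tolerated shortfall. The label is also on the wrong side, because non-inferiority belongs to the alternative.
- The sentence on the margin says when a shortfall counts as a difference. That is a rule for declaring inferiority and does not rule it out.
- The Introduction treats a non-significant difference as the result to be shown. Failure to reject a no-difference null is not evidence of non-inferiority, and it becomes easier to reach as fewer patients are analysed.

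The errors pull in opposite directions: the first, followed literally, makes success very unlikely when the methods are equal, and the third makes it too easy when self-tonometry is worse. What is at stake is which result counts as success on the primary endpoint.

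**Working it through.** **Inputs, all from Sample size.** Proportion with peaks 0.20 in each arm (the 20% figure is read as the assumed proportion, which the match below supports); margin 0.05; alpha 0.05; power 0.80. Allocation is 1:1 (Randomization).

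**1. Reproduce the stated sample size.** For H0: p_IG − p_CG ≤ −0.05 at one-sided alpha 0.05:

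n per arm = (1.645 + 0.842)² × (0.16 + 0.16) / 0.05² = 6.183 × 128 = 791.4, rounded up to **792**. Total 1584, and 1584 / 0.8 = **1980**. Both match exactly.

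Alternatives that do not match:
- non-inferiority at one-sided 0.025: 7.849 × 128, giving 1005
- difference test, 0.20 v 0.15: 714 (one-sided) or 906 (two-sided)
- difference test, 0.20 v 0.25: 862 or 1094

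Of the versions tried, only the margin-based test at one-sided 0.05 gives 792.

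**2. Operating characteristics of that test, 792 per arm.** With equal rates of 20%, SE = √(0.32 / 792) = 0.0201 and 0.05 / 0.0201 = 2.487. Power = Φ(2.487 − 1.645) = 80.0%. At the margin (15% v 20%) the simulated false-claim rate is 5.05% (400,000 runs).

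**3. Literal null without the margin.** At equal rates the truth lies on the boundary of this null, so a test at one-sided 0.05 rejects with probability **5%** (2.5% if two-sided), against 80% planned.

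**4. The Introduction's wording used as a rule.** At a true deficit of 5 points (15% v 20%), SE = √((0.1275 + 0.16) / 792) = 0.01905 and z = 0.05 / 0.01905 = 2.62. The probability of no significant difference is 1 − Φ(z − critical value):

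| Analysed per arm | Two-sided 0.05 | One-sided 0.05 |
|---|---|---|
| 792 | 25% | 16–17% |
| 990 | 17% | 10% |

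Simulation gives 25.5% and 16.5% in the first row. The intended rate is 5%. The rate rises as the analysed number falls.

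**5. Effect of the confidence level.** If non-inferiority is judged on the lower limit of a two-sided 95% interval (one-sided 0.025):
- 792 per arm: Φ(2.487 − 1.960) = 70.1% power
- 990 per arm: SE = 0.01798, and Φ(2.781 − 1.960) = 79.4% power
- 80% power needs 1005 per arm

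**The case against.** The strongest defence is that the sentences are loosely worded but the intended test can be recovered. The null has the correct direction, the margin appears shortly afterwards in the same section, and 792 reproduces exactly with the proper non-inferiority test. The Introduction's phrase follows directly on a statement that the aim is to demonstrate non-inferiority. The operational rule may sit in an analysis plan that is not shown, and its absence from an article is no fault.

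Much of this stands. The margin and the sample size are consistent and should not be called wrong. The absence of a full decision rule is not the point either. What remains is that the article names its null hypothesis and its primary hypothesis, and both are wrong as named. A correct analysis plan would contradict these statements and would not complete them.

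The defence also limits the numbers. A reader might take "by more than 5% to be taken as a statistically significant difference" as a rule on the observed difference, under which a truly 5-point-worse method would pass about half the time. The text does not mention an observed difference or set a point-estimate criterion. Another parse, non-inferior unless significantly worse than −5 points, gives about 95%. A figure that moves this far with the parse is not a property of the plan, so no rate is attached to that sentence.

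**Conclusion.** The point holds as an error in the stated hypotheses. The null lacks the margin and carries the wrong label, the margin is explained as a criterion for inferiority, and the Introduction puts non-significance in place of non-inferiority. Followed as written, these would give wrong conclusions, so they should be corrected before the data are analysed.

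The rates are illustrations under one reading each. The 5% success rate at equality assumes the margin-free null is tested at one-sided 0.05. The 25% false-claim rate assumes the Introduction's sentence is used as a two-sided 0.05 rule with 792 analysed per arm; other choices of sidedness and analysed number bring it down to about 10%, still above the intended 5%.

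A reader might infer that the trial's margin or sample size is wrong, or that the trial will run at these error rates. The documents support neither: 792 and 1980 follow exactly from the stated inputs under a correct non-inferiority test, and nothing shows that the literal wording was used in the design calculation.

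**What to change.** Replace the null-hypothesis sentence and the explanation of the margin in Sample size with:

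> H0: p_IG − p_CG ≤ −0.05; H1: p_IG − p_CG > −0.05, where p is the proportion of patients with at least one detected peak, tested at one-sided alpha 0.05. Non-inferiority is concluded only if the lower one-sided 95% confidence bound (the lower limit of the two-sided 90% interval) for p_IG − p_CG lies above −0.05. A non-significant difference is not taken as non-inferiority.

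Reword the primary hypothesis in the Introduction to agree, and check that any separate analysis plan says the same.

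The confidence level needs a deliberate choice, because Statistical analyses mentions 95% intervals. If the sponsor prefers the lower limit of the two-sided 95% interval, power should be restated as about 70% with 792 analysed per arm (about 79% with 990), and 80% would need 1005 analysed per arm.

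With the one-sided 95% bound the cost is wording only, with no new data and no change to the sample size. With the stricter limit the cost is the lower power or a larger sample.
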